### Randomization

Eligible participants will be randomly allocated to either the augmented MBCT with follow-up sessions group or MBCT without follow-up sessions group (1:1 ratio). A computer-generated random number stratified by diagnosis (ie, panic disorder/agoraphobia and social anxiety disorder) and baseline score for the STAI will be assigned to each participant. The Project Management Office at Keio Center of Clinical Research, which is an independent institution from the study group, will manage the randomization process. The flow of the recruitment of participants is shown in Figure 1.

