#### FFMQ

This tool is a self-report questionnaire that assesses mindfulness. It includes 5 factors, which are extracted on the basis of a factor analysis of 5 mindfulness questionnaires developed independently. The 5 facets are observing, describing, acting with awareness, not judging one’s inner experience, and not reacting to one’s inner experience. The total score ranges from 39 to 195, with higher scores representing a better mindfulness status [42].

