### Schedule for Assessments

All participants will be requested to fill the self-report measures at 4 weeks (the intervention midpoint) and 8 weeks (postintervention), and at 3, 6, and 10 months postintervention, as well as complete the baseline assessments. HAM-A and interoception will be assessed at baseline (0 weeks), at the end of the MBCT (8 weeks), and at 10 months postintervention. We will allow for a range of ±2 weeks from the scheduled evaluation date for the evaluation during the intervention period and ±4 weeks from the scheduled evaluation date for the evaluation during the follow-up period. For those who are unable to come to the hospital to complete the self-rated scales, we will contact them and ask them to fill out and return the above evaluation items by mail or telephone. The assessment schedule is presented in Table 2.

**Table 2 table2:** Schedule of assessments

	Study period																			
	Screening period	Intervention period									Follow-up period									
Timepoint		1 wk	2 wk	3 wk	4 wk	5 wk	6 wk	7 wk	8 wk	1 mo		2 mo	3 mo	4 mo	5 mo	6 mo	7 mo	8 mo	9 mo	10 mo
Screening (SCID^a^, etc)	✓																			
Informed consent	✓																			
MBCT with f/u^b^		✓	✓	✓	✓	✓	✓	✓	✓	✓		✓	✓	✓	✓	✓	✓	✓	✓	✓
MBCT without f/u^c^		✓	✓	✓	✓	✓	✓	✓	✓											
STAI^d^	✓				✓				✓				✓			✓				✓
PAS^e^	✓				✓				✓				✓			✓				✓
LSAS^f^	✓				✓				✓				✓			✓				✓
EQ^g^	✓				✓				✓				✓			✓				✓
SF-36^h^	✓				✓				✓				✓			✓				✓
SPANE^i^	✓				✓				✓				✓			✓				✓
RSES^j^	✓				✓				✓				✓			✓				✓
FFMQ^k^	✓				✓				✓				✓			✓				✓
CDRISC^l^	✓				✓				✓				✓			✓				✓
SCS^m^	✓				✓				✓				✓			✓				✓
QIDS^n^	✓				✓				✓				✓			✓				✓
GAD7^o^	✓				✓				✓				✓			✓				✓
PSS^p^	✓				✓				✓				✓			✓				✓
WHO-HPQ^q^	✓				✓				✓				✓			✓				✓
SWLS^r^	✓				✓				✓				✓			✓				✓
FS^s^	✓				✓				✓				✓			✓				✓
MAIA^t^	✓				✓				✓				✓			✓				✓
EQ-5D^u^	✓				✓				✓				✓			✓				✓
HAM-A^v^	✓								✓											✓
Interoception	✓								✓											✓
Health service use	✓				✓				✓				✓			✓				✓
Homework engagement		✓	✓	✓	✓	✓	✓	✓	✓	✓		✓	✓	✓	✓	✓	✓	✓	✓	✓

^a^SCID: Structured Clinical Interview for Diagnostic and Statistical Manual of Mental Disorders, 4th edition disorders.

^b^MBCT with f/u: mindfulness-based cognitive therapy with follow-up sessions.

^c^MBCT without f/u: mindfulness-based cognitive therapy without follow-up sessions.

^d^STAI: State-Trait Anxiety Inventory.

^e^PAS: Panic and Agoraphobia Scale.

^f^LSAS: Liebowitz Social Anxiety Scale.

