### Statistical Analysis

Statistical analyses and reporting of this trial will be conducted with primary analyses based on the intention-to-treat approach. The full analysis set will include all randomized subjects administered at least one procedure of the investigational treatment. For baseline variables, we will generate summary statistics with proportions and frequencies for categorical variables, and means and standard deviations for continuous data. Statistical data relevant to feasibility will be presented descriptively. For primary and secondary clinical outcome analyses, we will analyze mean changes from baseline with a restricted maximum likelihood-based repeated measures approach. The mixed model for repeated measures analyses will include the fixed and categorical effects of treatment, visit, and the treatment×visit interaction. We will employ Kenward-Roger approximation to estimate the degrees of freedom of the denominator. We will not conduct any adjustment for multiple testing of secondary outcomes because of the exploratory nature of the study. Imputation will not be performed for missing values because mixed models can deal with missing data by maximum likelihood. All comparisons are planned, and all P values are two-sided. A 5% significance level will be set for all statistical analyses. All statistical analyses will be conducted using Stata version 16 (Stata Corp).

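### The reason given for no imputation does not cover a missing baseline: with change from baseline as the response, such a patient leaves that outcome's model

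*Protocol article*

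**What the plan says.** All statements below are in the Statistical Analysis section of the protocol article unless another section is named.

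- Response: for primary and secondary clinical outcomes, "we will analyze mean changes from baseline with a restricted maximum likelihood-based repeated measures approach".
- Model terms: "The mixed model for repeated measures analyses will include the fixed and categorical effects of treatment, visit, and the treatment×visit interaction". No baseline covariate is listed.
- Analysis set: the primary analyses follow intention to treat, and "The full analysis set will include all randomized subjects administered at least one procedure of the investigational treatment". A baseline measurement is not a condition of entry.
- Missing data: "Imputation will not be performed for missing values because mixed models can deal with missing data by maximum likelihood". The missing-at-random condition is not mentioned.
- Randomization section: allocation is "stratified by diagnosis (ie, panic disorder/agoraphobia and social anxiety disorder) and baseline score for the STAI", so a baseline STAI score has to exist before a patient is allocated.

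**The concern.** The missing-data rule is stated without limit and rests on a single reason, that the mixed model deals with missing data. That reason is sound for a missed later visit, because the patient's other visits stay in the likelihood. It is not sound for a missing baseline. Every change score for that patient and outcome is then undefined, no row reaches the model, and maximum likelihood has nothing to work on.

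The patient is still in the full analysis set and may have completed every later assessment. For that patient, the promised intention-to-treat comparison and the stated model disagree. At stake are the model-based comparisons on the secondary scales, HAM-A and interoception in a trial of at most 50 patients. Descriptive means and SDs of raw scores at each visit need no baseline and are not affected.

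**Working it through.** **Inputs from the article**
- Maximum 50 patients, 25 per arm (Sample Size).
- Five post-baseline self-report assessments: 4 weeks, 8 weeks, and 3, 6 and 10 months after the intervention (Schedule for Assessments, Table 2). HAM-A and interoception have two.
- Response, model terms and missing-data rule as set out above.

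**Assumed input**
- The share d of patients without a baseline on a given outcome. The article gives no rate, so a range of 2% to 10% is used.

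The plan has no figure of its own to reproduce. Its sample size comes from a recommended range, not from a power or dropout calculation.

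**Step 1: what the model can use.** The response is Y(visit) − Y(baseline).
- Later visit missing, baseline present: one row is lost and the patient's other rows remain. Likelihood handles this under missing at random.
- Baseline missing: all rows are lost, whatever was observed later.

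**Step 2: counting records.** Suppose 3 of 50 patients lack a baseline (assumed) and all later visits are complete.
- Change-score model: 50 − 3 = 47 patients and 47 × 5 = 235 of 250 post-baseline records.
- Baseline kept among the responses: 50 patients and all 50 × 5 = 250 post-baseline records, plus 47 baselines, making 297 rows.

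A restricted maximum likelihood fit to simulated data gave the same counts: 47 patients and 235 rows, against 50 patients and 297 rows.

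**Step 3: effect on precision.** If losses are similar in the two arms, the standard error scales with the inverse square root of the number of contributing patients, so the factor is 1/√(1 − d).

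| Baselines missing (assumed) | Patients contributing, of 50 | SE factor |
|---|---|---|
| 0% | 50 | 1.00 |
| 2% | 49 | 1.01 |
| 5% | 47.5 | 1.03 |
| 10% | 45 | 1.05 |

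This compares losing these patients with having them complete. A patient with follow-up scores but no baseline carries less information than a complete one, so the part that can be recovered is at most about this size.

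**Step 4: STAI.** The baseline STAI score is needed for stratified allocation, so d should be close to 0 for the score used. The STAI section describes separate state and trait scales, and the Randomization section does not say which one stratifies. The protection is therefore large but not proven for both.

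**The case against.** Three points have weight.

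*The wording may already allow the better model.* Treatment, visit and their interaction also fit a model that has baseline among the repeated responses and estimates change as a contrast. That is possible, and the text does not settle it. Analysing "we will analyze mean changes from baseline" is more usually read as a change-score response. If the other model is meant, one clarifying sentence closes the point.

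*Baselines will rarely be missing.* Table 2 places baseline measures in the screening period, and for self-rated scales staff will contact patients who cannot attend and "ask them to fill out and return the above evaluation items by mail or telephone". This makes large losses unlikely for questionnaires. It does not cover the rater-administered HAM-A or the heartbeat task, which needs equipment attached to the patient. It limits the size of the problem but does not correct the reasoning.

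*The trial is exploratory.* Feasibility results are descriptive and secondary testing is unadjusted by design. This lowers the stakes and stands.

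A reader might also infer that a single blank item voids a questionnaire under the no-imputation rule, so that long forms would be lost in quantity. The article does not support that. The reason clause ties the rule to missing responses in the mixed model, and scoring a form comes before the model. Scoring rules for blank items are commonly left to the analysis plan or full protocol, so their absence from an article is no fault. Nor would one prorating threshold suit every scale: the QIDS converts 16 items into 9 domains, and the EQ-5D yields a single index.

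**Conclusion.** The point holds in a narrow form. The justification for no imputation is broader than the stated model supports. It fails for a missing baseline on any outcome other than, in the main, STAI, and in that case it conflicts with the intention-to-treat full analysis set.

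The size is small to modest: an SE factor of about 1.01 to 1.05 if 2% to 10% of baselines are missing. That range is assumed, and it takes losses to be similar in the two arms. The conclusion also rests on reading the response as a change score.

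It would go too far to say that patients are in fact being dropped, since no missingness rate is given, or that the primary clinical comparison is compromised, since stratification requires a baseline STAI score.

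**What to change.** Make two changes in the Statistical Analysis section.

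1. Limit the no-imputation sentence to missing assessments, and state that the likelihood analysis assumes they are missing at random.
2. Fit the repeated-measures model to the scores themselves, with baseline as one of the repeated responses and a common baseline mean across arms, and estimate each change and between-arm difference as a contrast. Restricted maximum likelihood and the Kenward-Roger approximation can stay.

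This keeps every patient with any observed score, including one with a baseline but no later visit. It also makes use of the baseline already collected, which the listed terms do not use beyond subtraction. Item scoring simply follows each instrument's own rules.

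The cost is about two sentences, with no new data and no added patient burden. The downside is a larger covariance matrix to estimate at about 25 per arm. If it is unstructured (an assumption, since the article names no structure), five visits need 5 × 6 / 2 = 15 parameters and six need 6 × 7 / 2 = 21. For HAM-A and interoception, the number goes from 2 × 3 / 2 = 3 to 3 × 4 / 2 = 6.

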### Subgroup Analysis

Considering the mixed participants in the study (those being offered face-to-face MBCT and the follow-up sessions online, and those being offered all sessions online), we intend to conduct a subgroup analysis sorted by participants receiving face-to-face MBCT and those receiving online MBCT.

### Adverse Events

When participants show serious adverse events, we will immediately contact the Ethics Review Committee at Keio University School of Medicine.

### Ethics

All procedures relevant to the study have been approved by the Ethics Review Committee of Keio University School of Medicine (reference number: 20190216). We have also ascertained that all procedures are in accordance with the ethical standards of the relevant national and institutional committees on human experimentation and with the Helsinki Declaration of 1975, as revised in 2008. The study is registered in the UMIN Clinical Trials Registry (UMIN000038626).

### Dissemination

We will present the results of the study at academic conferences, and the results are expected to be disseminated as articles in academic journals. The results of the study will comply with the CONSORT (Consolidated Standards of Reporting Trials) statement.

## Results

The study began to recruit participants in January 2020, and 43 participants have been enrolled up to January 2021. The intervention is ongoing and scheduled to be completed in February 2022. The participants in the first group (n=20) have been offered the 8-week MBCT intervention delivered in person. Owing to the COVID-19 pandemic, we were forced to switch to an online mode at the end of March 2020. Therefore, the participants in the first group were offered the face-to-face 8-week MBCT first, followed by online monthly follow-up sessions. For the second group (n=23), all interventions will be offered online. Data collection is expected to be concluded by May 2022.

## Discussion

The objective of this study is to investigate the long-term effectiveness of augmented MBCT with follow-up for anxiety disorders in comparison with MBCT without follow-up. Considering that the superiority of augmented MBCT posttreatment might not continue in the long term [30], developing a methodology to sustain its effectiveness in the long term is important. To the best of our knowledge, no studies to date have assessed the effectiveness of follow-up sessions after MBCT in comparison with MBCT alone. Therefore, this study is novel in terms of the design that compares augmented MBCT with and without follow-up sessions. Moreover, we expect our feasibility RCT to contribute to the development of well-designed definitive RCTs on the topic.

The limitations of our study are as follows. First, we expect differences in the participants included in the study in terms of the delivery of the intervention, as an impact of the COVID-19 pandemic (those offered face-to-face MBCT and online follow-up sessions, and those offered all sessions online). To account for the difference in the intervention delivery mode, we plan to conduct subgroup analysis. Second, we are not using a pharmacotherapy-alone arm. Thus, the study will not provide any implications regarding the clinical difference between augmented MBCT and pharmacotherapy alone. Nonetheless, considering that previous studies have already confirmed that augmented MBCT is superior to pharmacotherapy at posttreatment, we consider that our study design is acceptable from an ethical viewpoint. Despite the aforementioned limitations, we believe that this study will provide informative data for future clinical trials in this area.

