### Sample Size

For a feasibility study that involves evaluating the standard deviation of continuous variables, a sample size of 24 to 50 cases is recommended [75,76]. Therefore, in this study, the maximum number of enrolled patients has been set to 50 (25 for each arm).

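### Subgroup analysis by delivery mode does not account for mode in the overall comparison: the main model has no cohort term, and a split into 20 and 23 cannot show a mode effect

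*Protocol article*

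**What the plan says.** The Discussion treats the change of delivery mode as the first limitation and states the remedy: "To account for the difference in the intervention delivery mode, we plan to conduct subgroup analysis". The Subgroup Analysis section defines it: "we intend to conduct a subgroup analysis sorted by participants receiving face-to-face MBCT and those receiving online MBCT".

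The Statistical Analysis section lists the terms of the main model as "fixed and categorical effects of treatment, visit, and the treatment×visit interaction". It applies to mean change from baseline, and a two-sided 5% level is set for every analysis. The Randomization section stratifies a 1:1 allocation by diagnosis and baseline STAI. Neither section mentions delivery mode or cohort.

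The Results section gives the cohorts. "The participants in the first group (n=20) have been offered the 8-week MBCT intervention delivered in person". After the switch at the end of March 2020 their monthly follow-up sessions were held online. "For the second group (n=23), all interventions will be offered online". First and second group here mean successive cohorts, each containing both arms.

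**The concern.** The stated remedy does not do what the Discussion says it does. Sorting participants by mode gives results within each cohort. It leaves the overall arm estimate exactly as it was, because that estimate comes from a model without a term for mode or cohort.

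The split is also a poor tool for learning about mode. The cohorts are small. If each is tested at 5%, one significant and one non-significant result is not evidence that the effect differs. In addition, everyone in the first cohort had in-person MBCT and everyone in the second had online MBCT, with the change forced by a calendar date. Mode, cohort and period are therefore one variable.

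The trial is meant to inform a definitive RCT. A pair of subgroup results that disagree by chance could be taken as a finding about delivery mode and carried into that design.

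**Working it through.** **Inputs from the protocol article.** Cohorts of 20 and 23 (Results); cap of 50, 25 per arm (Sample Size); 1:1 allocation (Randomization); two-sided 5% and the model terms (Statistical Analysis).

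**Assumptions.** About 10/10 and 11/12 per arm within the cohorts, 21/22 overall, no dropout, one time point, effects in SD units. The article gives no SD, effect size or power.

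**1. The article's own figure.** 20 + 23 = 43, which agrees with "43 participants have been enrolled up to January 2021".

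**2. Overall comparison with and without a cohort term.** Without the term, the standard error (SE) of the arm difference is about sqrt[(1 + g² × v) × (1/21 + 1/22)]. Here g is the cohort difference in change and v is the variance of the cohort indicator, (20/43)(23/43)(43/42) = 0.255.
- g = 0: sqrt(0.0931) = 0.31 (simulation 0.30)
- g = 0.5: sqrt(1.064 × 0.0931) = 0.31
- g = 1.0: sqrt(1.255 × 0.0931) = 0.34

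With the term, the simulated SE is about 0.31 whatever g is. In the simulation both versions have a mean estimate of about 0 under no effect and a type I error near 5%. At a true effect of 0.5 SD and g = 1.0, power is 31% without the term and 36% with it.

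**3. Chance imbalance.** If mode is unrelated to the allocation strata, the number of face-to-face participants per arm is approximately hypergeometric (43 in total, 20 face-to-face, 21 in one arm). The counts differ between arms by 4 or more with probability 36%, and by 6 or more with probability 13%. The shift in the estimate from such a split is g times the difference in face-to-face proportions. For 12 of 22 against 8 of 21 and g = 0.5, it is 0.5 × (0.545 − 0.381) = 0.08 SD.

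**4. Within-cohort precision and power.**
- n = 20: half-width of the 95% CI = t(18) × sqrt(1/10 + 1/10) = 2.10 × 0.447 = 0.94 SD
- n = 23: t(21) × sqrt(1/11 + 1/12) = 2.08 × 0.417 = 0.87 SD
- Power at 0.5 SD (noncentral t): 18.5% and 20.8%
- Power at 0.8 SD: 39.5% and 44.8%

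**5. Discordant results when the effect is the same in both cohorts.** P(exactly one significant) = p1(1 − p2) + p2(1 − p1).
- 0.5 SD: 0.185 × 0.792 + 0.208 × 0.815 = 0.32
- 0.8 SD: 0.395 × 0.552 + 0.448 × 0.605 = 0.49
- No effect: 2 × 0.05 × 0.95 = 0.095

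**6. Direct contrast of the two effects.** SE = sqrt(1/10 + 1/10 + 1/11 + 1/12) = 0.61 SD; half-width = t(39) × 0.61 = 1.24 SD. Power is 13% if the effects truly differ by 0.5 SD and 36% if they differ by 1.0 SD.

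**7. Further enrolment.** The cap allows 50 − 43 = 7 more. If all join the online cohort (15/15), the half-width in step 6 becomes t(46) × sqrt(2/10 + 2/15) = 2.01 × 0.577 = 1.16 SD. The conclusion is unchanged.

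**The case against.** Much of the defence stands.

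- **Bias.** A reader might infer that the unadjusted main estimate is biased. The documents do not support this. Arms were randomised 1:1, so mode is independent of arm in expectation, and step 2 shows no bias and no inflation of type I error. The 0.08 SD in step 3 is the consequence of one assumed chance split and one assumed cohort difference. Because the model analyses change from baseline, that difference would have to lie in change, not only in baseline severity.
- **Precision.** At a cohort difference of 0.5 SD the SE is about 0.31 with or without the term. A visible gain needs a difference of about 1 SD.
- **Separate tests.** A reader might also infer that the plan commits itself to separate significance tests. It says only that the analysis is sorted by mode. Two tests at 5% is the most natural reading given the blanket significance level, but an interaction could stand in an analysis plan that is not shown. Steps 4 and 5 are conditional on that reading.
- **Design.** Not stratifying by mode was no fault, since in-person delivery was the initial plan. Both arms receive the 8-week MBCT, and the follow-up sessions were online in both cohorts. Mode therefore differs only in the phase that the arms share. This weakens the concern about the main comparison but does not rule out a different effect by cohort.
- **Setting.** This is a feasibility trial that calls itself exploratory and declares the limitation openly.

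None of this makes the stated remedy work. The claim in the Discussion and the listed model terms are both printed in the article, and they do not fit together.

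**Conclusion.** The point holds in a limited form. The subgroup analysis does not account for delivery mode in the overall comparison, because the stated model has no cohort term. The cost is chance imbalance and, only if the cohorts differ strongly, some precision: SE 0.34 against 0.31 SD at a difference of 1 SD.

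If the subgroup analysis is two within-cohort tests at 5%, a common effect of 0.5 SD leaves exactly one significant about 32% of the time. This rests on the assumed arm sizes, complete data and a single time point. No analysis of these data can separate mode from cohort and calendar period. In a feasibility trial the consequence is moderate, but the correction is nearly free and worth making.

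**What to change.** 1. In Statistical Analysis, add cohort (face-to-face MBCT then online follow-up; all online) as a fixed effect in the main model. A single term removes a constant cohort difference, not one that varies by visit.
2. In Subgroup Analysis, replace within-cohort significance tests with the treatment×cohort difference at 12 months and its 95% CI, taken from a supportive model with the needed interaction terms. Label it descriptive and confounded with calendar period. Its half-width of about 1.24 SD is wide, and it shows openly how little the data say about mode.
3. In the Discussion, say that subgroup analysis will explore the difference in delivery mode, and that adjustment comes from the cohort term.

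The cost is reworded text, one degree of freedom in the main model, and a slightly larger SE (about 0.31 against 0.30 SD) if the cohorts do not differ. No new data are needed.
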